#### 2.2.9. Anticipated Benefits and Disadvantages (Burdens and Risks)

Anticipated benefits: determining the optimal resection line using fluorescent clip markings may contribute to improved curability and the maintenance of postoperative function, including food intake.Anticipated disadvantages: The preoperative oral endoscopic marking and the intraoperative fluorescence measurement performed for research purposes will each involve a time commitment of approximately 30 min. Adverse events such as perforation, bleeding, tissue damage, and infection are mentioned in the package inserts of the Zemex FS Marker and Lumifinder™. However, the likelihood of such adverse events occurring owing to the use of these devices is extremely low, provided that endoscopic procedures and clipping are performed by endoscopy specialists and that the maintenance, cleaning, disinfection, and sterilization of the equipment and scope are conducted properly. If the fluorescent clip cannot be detected or is dislodged during surgery, additional intraoperative oral endoscopy may be required to determine the organ resection line, and the prohibition of MRI imaging after clip marking, as stated in the package insert, could potentially disadvantage the study participants.

#### 2.2.10. Handling of Adverse Events

Adverse events are any unfavorable or unintended injuries or symptoms (including abnormal clinical laboratory values) that occur in a research subject, whether or not they are related to the research that has been conducted, and that are recognized during the observation period from the day before the surgery marking.

When the investigator recognizes an adverse event, they will immediately take appropriate measures and provide treatment. The name of the adverse event, the date of onset and the date of resolution, the severity (mild, moderate, or severe), the outcome, the causal relationship with the study (related, unrelated), and the course of the event will be recorded. In addition, if the research device is discontinued or treatment for the adverse event is required, the research subject will be informed accordingly.

If the doctor in charge of the research becomes aware of the occurrence of any serious adverse event (death, life-threatening conditions, hospitalization or the prolongation of hospitalization, persistent or significant disability/incapacity, and any congenital anomaly in offspring), he/she shall take necessary measures, such as providing an explanation to the research subject and promptly reporting the event to the principal investigator. The principal investigator shall promptly report the event to the administrator of the medical institution of the relevant organization, take appropriate measures, and share information with the sub-investigator.

If an event that meets the conditions for an important adverse event (eczema, nausea, vomiting, etc., associated with fluorescent clip marking) occurs, the principal investigator will promptly report it, following the procedure for reporting serious adverse events. The principal or sub-investigator will appropriately record other adverse events in the medical record. 

#### 2.2.11. The Discontinuation or Termination of the Study

If a subject falls into any of the categories listed below, the principal investigator will promptly discontinue the subject’s participation in the study and take appropriate measures. Additionally, the investigator will monitor any adverse events identified during discontinuation and ensure the subject’s safety by performing necessary examinations and tests and providing appropriate medical care, contingent on the subject’s cooperation. The examinations conducted during discontinuation will be limited to those deemed medically relevant, respecting the subject’s autonomy and informed consent. Data relevant to the study will be collected promptly upon discontinuing the subject’s participation. In cases where a subject ceases to attend scheduled visits during the research period, the principal investigator will attempt to contact the subject via telephone or other means to encourage them to return for follow-up. If the subject cannot return to the hospital, their health condition will be assessed remotely through verbal communication. Any adverse events will be managed according to the relevant section’s protocol. The date and reason for discontinuation will be recorded in the Electronic Data Capture (EDC) system. The date of discontinuation will be defined as the date on which the principal investigator decides to terminate the subject’s participation in the study. The following are the criteria for discontinuation:Subject requests treatment modification or discontinuation—to uphold ethical considerations and respect for the subject’s autonomy.Observation of an adverse event that precludes continued participation—based on safety concerns.Occurrence of death or a life-threatening condition—to prioritize subject safety.Worsening of the primary disease—for the subject’s safety and well-being.Discovery of pregnancy—to mitigate the risks associated with potential harm to the subject or fetus.Deviation from the selection criteria or the violation of the exclusion criteria—to maintain the study’s integrity and validity.Failure to attend scheduled hospital visits—when continued participation cannot be assured.Confirmation of clip displacement via preoperative abdominal X-ray or intraoperative observation—rendering study continuation unfeasible.Other reasons deemed inappropriate by the principal investigator—based on professional judgment.

Criterion 1 was established to address ethical considerations, while criteria 2–5 and 6–9 were established to ensure subject safety and accommodate practical difficulties in continuing the study, respectively.

#### 2.2.12. The Discontinuation of the Entire Study

If any of the following situations arise, the principal investigator (PI) of the study shall consider suspending the entire study. If a suspension decision is made, the PI shall promptly notify all the responsible investigators in writing, including the reasons for the suspension. Furthermore, the PI shall submit a notice of the suspension of the entire study to the Certified Clinical Research Review Board (CRB) and the Minister of Health, Labour, and Welfare using the prescribed format within 10 days.

The PI shall promptly notify the administrators of the implementing medical institutions, as well as the research participants currently involved in the study. Additionally, appropriate examinations or interventions to confirm the safety of the research participants shall be conducted.

In cases where information is obtained that compromises, or may compromise, the ethical validity or the scientific rationality of the study that may affect the continuation of the study.In cases where information is obtained that compromises, or may compromise, the propriety of the study’s implementation or the reliability of the study’s results.In cases where it is determined that the anticipated risks of the study outweigh the expected benefits, or where information suggests that sufficient results have been achieved or will not be achieved through the study.In cases where significant information regarding the quality, safety, or efficacy of the research equipment is obtained, leading to the conclusion that the continuation of the entire study is not feasible.

If the study is suspended for any of the following reasons within the implementing medical institutions, the PI shall promptly notify the participating research subjects and conduct appropriate examinations or interventions to confirm their safety:If the Certified Clinical Research Review Board issues a recommendation or directive to suspend the study.If the Certified Clinical Research Review Board issues a directive to modify the study plan and it is deemed challenging to accept said modification.

#### 2.2.13. Termination of Research

The study is considered complete when the following tasks are fully accomplished:The completion of subject enrollment and observation periods.The preparation of the primary endpoint report, the final study report, and the summary of the final report.The submission of the primary endpoint report to the Ministry of Health, Labour, and Welfare.The submission of a summary of the final report, study protocol, and statistical analysis plan to the Ministry of Health, Labour, and Welfare.The submission of the primary endpoint report, the final report, and the summary of the final report to the administrators of the participating medical institutions.The registration of the summary of the study results in the jRCT.The notification of the administrators of the participating institutions regarding the publication of the study results.

#### 2.2.14. Reporting of Protocol Deviations

When the principal investigator becomes aware that the study is not in compliance with the Clinical Research Act (including enforcement regulations and related notifications) or the research protocol (hereinafter referred to as “non-compliance”), they shall promptly report this to the Director of Hokkaido University Hospital. If a sub-investigator identifies a protocol deviation, they shall promptly report it to the principal investigator.

If the principal investigator determines that a deviation is particularly serious, they must immediately report it to the certified clinical research review committee. Additionally, they must implement measures to prevent recurrence and ensure future compliance.

In the event of a change in the principal investigator, the research and implementation plans must be revised. This revision requires a review by the certified clinical research review committee and that the Minister of Health, Labour, and Welfare be notified of the implementation plan. Consequently, completing these procedures may take a certain amount of time. Furthermore, in some instances, the change may not be announced until just before it takes effect, making it challenging to finalize the procedural requirements in advance.

Therefore, even if the principal investigator is temporarily absent due to the change, the study does not constitute a “deviation” if the research management system is maintained by the sub-investigators and the medical care system for enrolled patients is ensured.

#### 2.2.15. Post-Research Actions

After the completion of this study, the medical care considered most appropriate for the subjects will be provided, incorporating the findings obtained from this research.

#### 2.2.16. Data Collection

In this study, the EDC system will be used to record the necessary information. The principal investigator and the administrator of the medical institution where the study will be conducted will ensure that the data in the case report forms and all other reports are accurate and complete.

#### 2.2.17. Case Report Form Creation (EDC System Input) and Storage Management

The principal investigator will prepare a “case report form entry guide” that explains the entry procedures and notes on completion, etc., if necessary. The person completing the case report form will enter the data into the EDC system in accordance with the “case report form entry guide”. Hereafter, case report form completion will be referred to as EDC system entry.

The investigator will enter data into the EDC system as the study progresses for all the subjects enrolled until the study is completed.

When entering data into the EDC system, a number (subject identification) that is not related to the personal information of the research subject will be assigned, and a correspondence table with the registration numbers will be created so that the data and individuals can be identified. Still, this correspondence table will not be provided and will be kept at the medical institution where the study is conducted. It will not contain any information that could identify the research subjects.

#### 2.2.18. Monitoring

The monitoring of this research shall be carried out in accordance with the Monitoring Procedures. In addition, the principal investigator and the institution implementing the study will ensure that all the records related to the research subjects are readily accessible for direct review upon request by the monitoring personnel. The monitoring personnel shall confirm that the research is being conducted in adherence to the Clinical Research Act, applicable notifications, and the approved research protocol.

## 3. Expected Results and Discussion

Fluorescent clip-based tumor marking is one of the most promising methods for intraoperative identification during GI cancer surgery. However, Kumagai et al. reported that in fluorescent clip-based tumor marking using the current imaging system for gastric cancer surgery, the detection rate of the fluorescent clips was only 75%, which is significantly lower than the identification rate of tumors and clips (100%) using intraoperative endoscopy [16]. The primary cause of this low detection rate is thought to be the limitation of the current NIR fluorescent imaging system, which can only observe tissue thicknesses of 5–10 mm, whereas the gastric wall can sometimes be over 10 mm thick [17,19,20].

Our newly developed fluorescence detection system, “Lumifinder™”, enables the higher-sensitivity detection of fluorescence by analyzing the spectral characteristics of fluorescence and measuring peak values. In fact, it has successfully detected fluorescent clips in a porcine stomach with a thickness of 13 mm [18], and its usefulness has been reported in several clinical trials [21,22]. We expect that this new system will be able to detect fluorescent clips with a high probability, regardless of the thickness of the organ wall or the lesion’s location. This method will enable the determination of resection lines that balance curability and functionality, even in facilities where intraoperative endoscopy is challenging. In certain cases, fluorescent clips may not be detectable because of their inherently low fluorescence intensity. Given our extensive synthesis of noble NIR fluorophores and the reported outcomes of their clinical performance in preclinical settings [23], we are confident of our ability to develop a novel fluorescent clip with a significantly enhanced fluorescence intensity in future studies.

However, this ideal marking method has certain drawbacks. Because our spectral system does not objectively display fluorescent signals like an imaging system, it requires “exploration” to locate the fluorescent clips. As a result, detecting the signals may take longer than with traditional imaging systems in some cases. In this study, observations using the existing near-infrared fluorescence imaging systems are also planned as a reference. However, a prospective comparative study between our new fluorescence detection system and the near-infrared fluorescence imaging system will be necessary to determine the future standard of care.

Additionally, distinguishing whether the clip is on the anterior or the posterior wall is challenging. To compensate for these limitations, thorough preoperative imaging is necessary to confirm the lesions.

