## Abstract

**Background**: Determining the optimal resection line for an organ that cannot be palpated is crucial, but challenging, in minimally invasive gastrointestinal (GI) surgery. Therefore, there is an urgent need to establish the most effective method for tumor localization. We hypothesize that our novel near-infrared (NIR) fluorescence detection system will enable the highly accurate detection of fluorescent clips marking GI cancer. **Methods**: Twenty-five patients with gastric cancer, esophagogastric junctional cancer, or esophageal cancer will be enrolled. NIR fluorescent clips will be placed endoscopically around the tumor on the day before surgery. Patients in whom clip dislodgement is confirmed by preoperative abdominal radiography will be excluded. The clips will be placed before the transection of the organ, and those on the surgical specimen will be observed after transection using both the novel NIR fluorescence detection system and an existing NIR fluorescence imaging system. The detection rate and time, the fluorescence intensity, surgical margins, and adverse events will be evaluated. This study has been registered in the Japan Registry of Clinical Trials, with the code jRCTs012240043. (**Expected**) **Results**: As the novel fluorescence detection system allows for higher-sensitivity detection by analyzing the spectral characteristics of fluorescence and measuring the peak values, we anticipate that this new system will detect the fluorescent clips with high accuracy. **Conclusions**: This study aims to establish a novel tumor-marking method using fluorescent clips and a new detection system that can be easily applied in various medical facilities.

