#### 2.1.2. Intraoperative Procedures

Immediately after initiating laparoscopic, thoracoscopic, or robotic procedures, the surgeon uses the NIR fluorescence detection system to locate the NIR fluorescent clips on the target organ. The probe tip should be positioned 4 cm from the target organ and applied as perpendicularly as possible to the organ in order to excite and detect the fluorescence of the clips. The quantification of the fluorescence of the clips and the measurement of the detection time are recorded.As a reference, the NIR fluorescent clips are examined using an existing NIR fluorescence imaging system. In laparoscopic and thoracoscopic surgery, the endoscope is equipped with a fluorescence observation mode. This endoscope is also used in robotic surgery for fluorescence observation, allowing the study to be conducted under similar conditions.If the fluorescent clip cannot be detected, the endoscopist performs an additional intraoperative oral endoscopy.After these examinations, the gastric cancer, esophagogastric junctional cancer, or esophageal cancer is resected in the usual manner.

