#### 2.2.4. Endpoints

The primary endpoint of this study is to determine whether the Lumifinder™ can detect the XEMEX FS Marker^®^ around the tumor. Secondary endpoints include assessing the variation in signal intensity at different tumor locations, differences in the thickness of the gastric or esophageal wall, the time required for clip identification and fluorescence measurement, and the measurement of the proximal and distal margins of the surgical specimen. The safety endpoint involves evaluating any adverse events associated with the use of Lumifinder™ and the XEMEX FS Marker ^®^.

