#### 2.2.8. Statistical Analysis Methods

The patients’ demographic and baseline characteristics will be described using appropriate statistical measures: the mean and the standard deviation or the median and the interquartile range, as needed, for the continuous data and the frequency with the percentage for the categorical data. For the primary endpoint, the success rate and a 95% confidence interval will be calculated using the Wilson’s score method. The secondary endpoints will be analyzed by estimating values with corresponding 95% confidence intervals, and the relationships among the variables will be assessed using visual and statistical tools such as scatter plots, box plots, and Pearson’s correlation coefficients, among others, as appropriate. Cases in which all the clips are confirmed to have been dislodged during preoperative abdominal radiographs or intraoperative evaluations will be excluded from the statistical analysis.

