## 4. Conclusions

This study will be conducted with the aim of establishing a novel tumor-marking method utilizing fluorescent clips and an innovative fluorescence detection system. This approach is more reliable, simpler, and less invasive than the existing methods and can be implemented in a wide range of medical facilities. Therefore, it is expected to become the standard technique for minimally invasive GI surgery.

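### The claims concern a marking method, but patients who lose all clips leave the analysis, so success over all marked patients is not estimated

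*Protocol article*

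**What the plan says.** **Aim and claim.** Section 4 (Conclusions) states: "This study will be conducted with the aim of establishing a novel tumor-marking method utilizing fluorescent clips", together with the new detection system. Section 3 extends this to places where endoscopy during surgery is hard to arrange: "This method will enable the determination of resection lines that balance curability and functionality, even in facilities where intraoperative endoscopy is challenging". The Abstract also gives a marking method as the aim.

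**Endpoints.** Section 2.2.4 makes detection of the clip by Lumifinder the primary endpoint. The secondary list begins "Secondary endpoints include assessing the variation in signal intensity at different tumor locations, differences in the thickness of the gastric or esophageal wall" and goes on to times and surgical margins; a safety endpoint follows. Clip loss and fallback endoscopy are not listed.

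**Analysis set.** Section 2.2.8 sets the rule for patients left without any clip: "all the clips are confirmed to have been dislodged during preoperative abdominal radiographs or intraoperative evaluations will be excluded from the statistical analysis". The rule applies to the analysis as a whole, not only to the primary rate. The Abstract is worded more broadly: "Patients in whom clip dislodgement is confirmed by preoperative abdominal radiography will be excluded". Section 2.2.11 makes clip displacement, seen before or during surgery, a reason for discontinuation, and has that reason entered in the EDC system.

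**Fallback.** Section 2.1.2: "If the fluorescent clip cannot be detected, the endoscopist performs an additional intraoperative oral endoscopy". Section 2.2.9 adds that when a clip is not detected, or comes off during surgery, "additional intraoperative oral endoscopy may be required to determine the organ resection line".

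**The concern.** Two quantities are in play. One is a device property: given a clip in place, does Lumifinder find it? The other is a method property: of the patients who had clips placed, in how many was a clip both retained and found? The plan estimates the first. The statements in sections 3 and 4 are about the second.

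A clip that falls off before the detector is used says nothing against the detector, so leaving that patient out of the device rate is defensible. It is still a failure of the marking method, because the surgeon has no fluorescent mark to work from. A hospital that cannot easily provide intraoperative endoscopy would want the proportion over everyone marked. The plan expects some losses, since it enrols 25 to secure 21 partly because of dislodgement, but it plans no estimate that includes them.

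The point does not depend on how dislodgement is verified. It would stand even if every such judgement were correct.

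**Working it through.** **Inputs**
- Analysed patients required: 21. Enrolled: 25. The difference of 4 covers clip dislodgement and ineligible cases together (section 2.2.7).
- Assumed success rate 90%; target 95% interval width below 30%, to be met with probability 80% or more (section 2.2.7).
- Wilson score interval for the primary rate (section 2.2.8).
- Clip-loss rate: not given. Assumption: all 25 have clips placed and 0 to 4 lose every clip.

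**Step 1. Reproduce the plan's 21.** With z = 1.96, p = x/n and D = 1 + z²/n, the Wilson limits are

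(p + z²/2n)/D ± z·√[p(1−p)/n + z²/4n²]/D.

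At n = 21 the width is 0.297 for x = 18 and 0.323 for x = 17, so the target is met when x ≥ 18. The binomial probability of that at 90% success is 0.848. At n = 20 the probability of meeting the target is 0.677. The smallest n that reaches 0.80 is 21, as stated. The sample size is correct for detection given a retained clip.

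**Step 2. Expected rate over all marked patients.** With 90% detection among retained clips it is 0.9 × (1 − loss):
- loss 0%: 90.0%
- loss 4% (1/25): 86.4%
- loss 8% (2/25): 82.8%
- loss 12% (3/25): 79.2%
- loss 16% (4/25): 75.6%

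**Step 3. The same in whole patients.** Detected = 90% of those retained, rounded: 22.5→22, 21.6→22, 20.7→21, 19.8→20, 18.9→19.

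| Lost all clips | Rate as planned (Wilson 95%) | Rate over all marked (Wilson 95%) | Gap, points |
|---|---|---|---|
| 0 | 22/25 = 88.0% (70.0–95.8) | 22/25 = 88.0% (70.0–95.8) | 0 |
| 1 | 22/24 = 91.7% (74.2–97.7) | 22/25 = 88.0% (70.0–95.8) | 3.7 |
| 2 | 21/23 = 91.3% (73.2–97.6) | 21/25 = 84.0% (65.3–93.6) | 7.3 |
| 3 | 20/22 = 90.9% (72.2–97.5) | 20/25 = 80.0% (60.9–91.1) | 10.9 |
| 4 | 19/21 = 90.5% (71.1–97.3) | 19/25 = 76.0% (56.6–88.5) | 14.5 |

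Worked example for 19/25: D = 1 + 3.8415/25 = 1.1537; centre = (0.76 + 0.0768)/1.1537 = 0.725; half-width = 1.96 × √(0.007296 + 0.001537)/1.1537 = 0.160; limits 0.566 and 0.885, width about 0.32. For 19/21 the width is 0.263.

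The planned rate hardly moves as losses rise, because each loss leaves the numerator's potential and the denominator together. The all-marked rate falls with every loss.

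**The case against.** **The device rate is properly conditional, and the trial is exploratory.** Agreed. Section 2.1 calls it exploratory, the hypothesis in the Introduction is about detection, and section 3 says that a comparative study is still needed. The primary endpoint should stay as it is. What remains is the gap between that rate and the unqualified statements in sections 3 and 4.

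**The full analysis plan may report clip loss as patient flow.** It may, and section 2.2.11 records the reason for discontinuation, so a tally is possible. But the endpoint list and the exclusion are stated outright, and an analysis that follows section 2.2.8 as written would not include these patients in any estimate.

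**Fallback is already visible.** Partly true. Section 2.1.2 ties endoscopy to non-detection, which is the complement of the primary endpoint among analysed patients. It would be wrong to say that fallback is never captured. What no endpoint captures is clip loss and whatever follows it.

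**Two stronger readings are tempting and should not be drawn.**
- A reader might infer that at 4 lost, 6/25 = 24% would need fallback endoscopy. The documents do not support this. Section 2.1.2 concerns clips that cannot be detected. Section 2.2.9 concerns non-detection or loss during surgery, and says only that endoscopy may be required. For loss seen on the preoperative radiograph, section 2.2.11 discontinues the patient and does not mention endoscopy.
- A reader might set 76% beside the 75% that section 3 quotes for current imaging and conclude that nothing is gained. The 75% is described as a clip detection rate. The article does not say whether it is per clip or per patient, or how lost clips were treated, so the two are not comparable.

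**Conclusion.** The point holds in a limited form. The stated exclusion, with no endpoint for clip loss, leaves detection given a retained clip as the only efficacy rate. Success of the marking method over all marked patients is not estimated, although sections 3 and 4 make claims about the method.

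The gap runs from nothing at 0 lost, through 91.3% against 84.0% at 2 lost, to 90.5% against 76.0% at 4 lost. This rests on three assumptions: all 25 have clips placed; detection among retained clips is about 90%, as the plan assumes; and complete loss affects 0 to 4 patients. Four is an upper bound, because the same allowance covers ineligible cases. Only complete loss is counted here. Under section 2.2.8 patients with partial loss stay in; the wording in the Abstract and section 2.2.11 is broader and needs reconciling with it.

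The primary analysis and the sample size of 21 are unaffected. This is an inexpensive improvement in what the trial reports, not an error in its main result.

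**What to change.** 1. Keep the Lumifinder detection rate as the primary endpoint, and limit the exclusion in section 2.2.8 to that rate.
2. In sections 2.2.4 and 2.2.8 add a descriptive secondary result over all patients who had clips placed: the proportion with a clip retained and detected by Lumifinder, with complete clip loss at any time counted as not achieved, and a Wilson 95% interval.
3. Report beside it the proportion who lost all clips and, where recorded, the number who had intraoperative endoscopy.
4. Rest the statements in sections 3 and 4 on this rate, or soften them.

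**Cost.** A few sentences, no added patients and no added procedures. Clip loss can be taken from the radiograph result and the discontinuation reason in the EDC system. The article does not show that later endoscopy is recorded for discontinued patients, so that count may be incomplete and should be labelled so. The method-level figure may be less favourable than the device rate, and its interval somewhat wider: about 0.32 at 19/25, just above the 0.30 that the plan set for the device rate.
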